#### Foot care-related costs

Healthcare resource use of participants will be determined using the Institute for Medical Technology Assessment (iMTA) Medical Consumption Questionnaire (iMCQ) [42]. Cost prices will be calculated according to the 2015 Dutch guideline for health economic evaluation [43]. If relevant, costs of medication use will be derived from the Dutch formulary increased with a pharmacist’s charge. Costs of diagnostic tests will be based on Dutch tariffs, and, if applicable, costs of over-the-counter medication and alternative medicines will be based on average retail prices. Costs of consulting a general practitioner or medical specialist or other procedures and hospitalizations will be based on the 2015 Dutch guideline for health economic evaluation [31] or charges if no other estimates are available. The potential productivity losses from complications of the foot or the orthopedic shoes will be assessed using the iMTA Productivity Cost Questionnaire (iPCQ) [44] instrument among all participants at baseline and 12 months after baseline, and additionally among participants who present with complications, at 4 weeks after the complication was diagnosed [32]. A friction cost approach will be applied to estimate the productivity losses as defined in the Dutch costing manual and based on the reference costs of not being able to perform paid or unpaid work.

### Participant timeline {13}

An overview of the study design and the main procedures that participants will undergo during the course of the study are shown in Table 2. The participant will receive the novel care approach or usual care. All standardized instruments used in the study procedure are described in Table 2.

The participants will be followed from inclusion up to 12 months after receiving their orthopedic shoes, with visits planned at different moments during this period for consultations with the podiatrist, pedorthist, and investigator. During every study consultation with the investigator, the participant will be asked about complications.

#### Time point “− T2”—screening

Eligible patients, who will be referred to the pedorthist for orthopedic shoes, will be informed about the study by the podiatrist and will receive the information brochure and informed consent form. The podiatrist will ask permission to send contact details to the research team. On receipt of that permission, the podiatrist will provide details of the patient to the coordinating investigator. The coordinating investigator will contact the patient in order to further explain the study and answer any questions the patient may have. After this contact, the patient will be given a minimal 1 week to decide to participate in this study.

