#### Concealment mechanism {16b}

The participants have not randomized themselves, because the background assignment of the treating podiatrist (being trained in MI or not) will determine the treatment allocation of the participants. Randomization is performed at the level of the podiatrists to avoid contamination between intervention and control participants. Therefore, the randomization sequence will not be concealed from the podiatrists. Because each podiatrist will exclusively provide either the MI intervention or usual care, and thereafter, the pedorthist will provide the new digital shoe-fitting procedure for the intervention group of participants or the casting-based shoe-fitting procedure for the control group, and the randomization sequence will also not be concealed from the pedorthists.

All participant data is pseudonymized, but because the investigators have access to the coding of the personal data of the participants, the randomization sequence will also not be concealed from them.

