### Assignment of interventions: blinding

#### Who will be blinded {17a}

Blinding and concealed treatment allocation for podiatrists is not feasible, because of the way of randomization (see the “Concealment mechanism {16b}” section). Outcome assessments and analyses are not performed by independent staff, but by the investigators themselves, and therefore, they are also not blinded to the treatment allocation (see the “Concealment mechanism {16b}” section).

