Second, due to this new role of the pedorthist, the background assignment of the treating podiatrist (being trained in MI or not) no longer determines the shoe-fitting procedure by the pedorthist. Each pedorthist has his/her own procedure of shoe-fitting: the new digital shoe-fitting procedure or the casting-based shoe-fitting procedure. In addition, the existing last is also used for an extra pair of orthopedic shoes, and thereby the shoe-fitting procedure is already determined for each subsequent pair of orthopedic shoes. However, the background assignment of the treating podiatrist remains leading over the shoe-fitting procedure with regard to which group the participant belongs to (intervention or control group), because most participants have been treated by the same podiatrist for years and we do not want to change that for this study. The participants in the intervention group will have an appointment with their podiatrist or one of the other MI-trained podiatrists to perform motivational interviewing before or as soon as possible after they receive their first or new pair of orthopedic shoes.

Last, the second group of 12 additional podiatrists received MI training, and 16 podiatrists have been added to the control group to further increase inclusion. Because the inclusion in the intervention group lagged behind the control group, the second group of podiatrists, who received MI training, consists of the podiatrists who see most patients with diabetes. This is in contrast to the original group of podiatrists, who were assigned to one of the groups based on stratified randomization.

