## Trial status

The first version of this study protocol (22 January 2019) was registered at The Netherlands Trial Register (registration number NL7710, https://www.trialregister.nl/trial/7710) on 6 May 2019. The trial commenced recruitment in July 2019. Inclusion is currently ongoing and expected to be completed in December 2020.

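### Patients are recruited after podiatrists are randomised, by podiatrists and now pedorthists who know the allocation, so the arms can differ in willingness to wear the shoes before any intervention

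*Protocol article*

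**What the plan says.** All references are to the protocol article.

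- **Allocation comes first.** *Sequence generation {16a}* randomises podiatrists. *Concealment mechanism {16b}* says the treating podiatrist's assignment determines the patient's arm.
- **The podiatrist makes the first approach.** *Time point − T2, screening*: "Eligible patients, who will be referred to the pedorthist for orthopedic shoes, will be informed about the study by the podiatrist". The podiatrist hands over the brochure and consent form, and then: "The podiatrist will ask permission to send contact details to the research team". *Recruitment {15}* repeats this.
- **The podiatrist knows the arm.** *Concealment mechanism {16b}*: "Therefore, the randomization sequence will not be concealed from the podiatrists". *Who will be blinded {17a}*: "Blinding and concealed treatment allocation for podiatrists is not feasible, because of the way of randomization".
- **The next contact is not concealed either.** *Screening*: "The coordinating investigator will contact the patient in order to further explain the study and answer any questions the patient may have". Of the investigators, *Concealment mechanism {16b}* says "the randomization sequence will also not be concealed from them". It says the same of the pedorthists.
- **A second route was added.** The *Discussion* reports that patients who already have orthopedic shoes are now eligible and that the pedorthist actively recruits.
- **Inclusion has differed by arm.** *Discussion*: "Because the inclusion in the intervention group lagged behind the control group". In response, 12 more podiatrists, chosen for their diabetes caseload, were trained in motivational interviewing (MI), and 16 were added to the control group.
- **Recruitment is open.** *Trial status*: "Inclusion is currently ongoing and expected to be completed in December 2020".
- **Analysis.** *Primary study outcome* specifies a logistic mixed model with random effects for podiatrists and names no baseline covariate. *Descriptive statistics* plans significance tests of baseline characteristics.

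**The concern.** This is a cluster trial with recruitment after randomisation by people who know the allocation. On the podiatrist route, a patient who is not offered the study, or who declines to have details passed on, never reaches the research team. The podiatrist therefore influences who enters.

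The recruitment conversation can itself differ by arm. *Motivational interviewing training of podiatrist* says trained podiatrists are to use the techniques in their consultation hours, and the referral consultation is one of these. The background section says wearing the shoes depends on intrinsic motivation. The characteristic most open to selection is thus one that the protocol links to the primary outcome.

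If the arms come to differ in willingness to wear the shoes, part of the observed difference in adherence reflects who was recruited and not what was delivered. Randomising podiatrists does not protect against this, because selection happens afterwards. A random podiatrist effect describes variation between podiatrists within an arm; it does not correct a shift shared by the podiatrists of one arm.

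**Working it through.** **Step 1. The plan's own figure.** Inputs from *Sample size {14}*: 40% v 60%, two-sided alpha 0.05, power 0.80, intraclass correlation 0.01, 200 in total before dropout. *Sequence generation {16a}* gives 20 podiatrists, so 200/20 = 10 patients each.

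- Per arm, unpooled variance: (1.960 + 0.842)² × (0.24 + 0.24) / 0.20² = 94.2.
- Design effect: 1 + (10 − 1) × 0.01 = 1.09. Then 94.2 × 1.09 = 102.7, so 103 per arm and 206 in total.
- Power at 200 in total: Φ(0.20/√(0.48 × 1.09/100) − 1.96) = 0.79.

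The stated 200 is reproduced closely enough and is not disputed. It says nothing about selection.

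**Step 2. Standard error for the illustration.**

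- Analysed per arm: 110 × (1 − 10/171) ≈ 103.5.
- Podiatrists now: 20 + 12 + 16 = 48. Patients each: 207/48 = 4.3. Design effect: 1 + 3.3 × 0.01 ≈ 1.03.
- SE = √(2 × 0.24 / 103.5 × 1.03) = 0.069.

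**Step 3. Effect of a recruitment imbalance when there is no treatment effect.** Two quantities are assumed, because the documents give neither: the gap in adherence between motivated and other patients, and the difference between arms in the share of motivated patients.

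Shift b = gap × difference in share. Rejection probability = 1 − Φ(1.96 − b/SE) + Φ(−1.96 − b/SE).

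| Assumed gap | Assumed difference in share | Shift b | b/SE | Type I error |
|---|---|---|---|---|
| 20 points | 5 points | 1 point | 0.14 | 5.2% |
| 20 points | 10 points | 2 points | 0.29 | 6.0% |
| 40 points | 10 points | 4 points | 0.58 | 8.9% |
| 40 points | 15 points | 6 points | 0.87 | 14.0% |

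A 4-point shift is one fifth of the planned 20-point effect. With 100 per arm, design effect 1.09 and 40% adherence in the control arm, a 4-point shift gives 8.5%, so the result depends little on the standard error used.

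**Step 4. What the documents can say about the actual shift.** Nothing on size or direction. The *Discussion* reports the lag without counts by arm, numbers approached or a reason.

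**The case against.** Several points on the other side have weight.

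- **The lack of concealment is disclosed and reasoned.** Podiatrists are randomised to avoid contamination, and they cannot then be blinded. That stands. It does not require that they decide who is approached, or in what words.
- **The lag may be only a matter of volume.** A reader might infer that slower inclusion in the intervention arm shows selective recruitment. The documents do not support this: caseload or logistics could explain it, and adding high-caseload podiatrists is a response to volume.
- **Motivation may be measured at baseline.** A reader might infer that it is not recorded. *Outcomes {12}* lists behavioral intentions at inclusion, and *Time point − T1* records capacity for self-care and history of shoe use. Table 2 is not shown. On the other hand, *Experiences of participant* places the shoe questionnaire at 6 and 12 months and the baseline interviews in 30 participants only. A measure in everyone is therefore uncertain, neither established nor excluded.
- **A selection effect need not be inseparable from the treatment effect.** A reader might go that far. Counts by arm and any baseline measure would help to judge it.
- **A screening log may exist in the full protocol.** This is fair, and its absence from an article is no finding. The point rests on the recruitment procedure that is stated.
- **Shifting the explanation to the investigator does not restore concealment.** Correct, since the investigator is not concealed either. A fixed script limits differences in what is said; it does not blind anyone.

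**Conclusion.** The point holds as a risk built into the stated procedure. Recruitment follows allocation, those who make the first approach on both routes know the allocation, the next contact is not concealed, and the primary model does not remove selection that runs with arm.

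Whether selection has occurred, in which direction and how strongly, cannot be judged from the documents. The illustrated type I error runs from about 5% at a 1-point shift to about 9% at 4 points and about 14% at 6 points. It rests wholly on assumed gaps and imbalances, no true effect, and equal arms of about 103.5 analysed patients. The change is cheap while inclusion is ongoing and should be made.

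**What to change.** For the rest of recruitment:

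1. Give the same arm-neutral written text to every consecutive eligible patient on both routes: podiatrist referrals, and patients whom the pedorthist sees for a repeat pair. A list of podiatrist referrals alone may miss the second group.
2. Keep the existing step in which the patient permits contact details to be passed on.
3. Have the coordinating investigator, who already contacts candidates, give the substantive explanation from one fixed script used in both arms.
4. Log eligible, offered and consenting patients per podiatrist and per pedorthist.

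For patients already recruited, compile the same counts retrospectively where referral lists allow; the documents do not describe these lists, so coverage may be partial.

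Report approach and consent rates by arm, and by randomised versus added podiatrists, beside the primary result.

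The cost is slightly more administration by existing staff. The prospective steps reach only patients still to be recruited, with completion expected in December 2020. The counts show whether selection is plausible; they cannot remove bias among patients already included.

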#### Time point “− T1”—inclusion

After referral of the podiatrist, the pedorthist and medical specialist will decide together, during a multidisciplinary consultation, which type of shoes the patient will need. When instead of custom-made orthopedic shoes convection shoes or semi-orthopedic shoes will be prescribed, the patient cannot be included in the study. After the patient has been prescribed custom-made orthopedic shoes, he/she will be asked if he/she decided to participate in this study, and the investigator or the investigator’s representative will ask the patient to sign informed consent. Also, the demographic data (age, gender, ethnicity, height, and weight), diabetes type and duration, risk profile, ambulatory status, history regarding the use of orthopedic shoes, educational status, socioeconomic status, and capacity for self-care are completed. Subsequently, data on the presence of peripheral artery disease, peripheral neuropathy, foot deformities, and history of previous foot ulceration and amputation will be recorded, and the participants will be asked to fill in specific questionnaires (time point “− T1” at Table 2).

Thereafter, during a consult with the pedorthist, the orthopedic shoes will be fitted. The pedorthist will provide the new digital shoe-fitting procedure or the casting-based procedure depending on whether the podiatrist is trained in MI or not.

Within 1 to 6 weeks, the participant from the intervention group will have another consultation with the MI-trained podiatrist (first consult: participant was referred to the pedorthist). The podiatrist will apply MI in this conversation. From all included participants, thirty participants, 15 from both groups, will be approached for an in-depth interview about their perspective on and experiences with orthopedic shoes before receiving these shoes. This interview will be performed by one of the investigators.

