### Outcomes {12}

The primary outcome is the proportion of participants who adhere to wearing their orthopedic shoes (see the “Proportion participants being adherent” section). We define adherence as minimally 80% of daily steps taken with orthopedic shoes based on the data of a randomized trial in The Netherlands [13, 14].

Secondary outcomes are 1) the level of adherence to wearing orthopedic shoes during 1 week at 3 and 6 months after inclusion; 2) the change in adherence between 3 and 6 months after inclusion; 3) total wearing time during 1 year follow-up; 4) the proportion of participants (re-)experiencing complications during 1 year follow-up; 5) the participant-perceived quality of life at inclusion and 3 and 6 months after inclusion; 6) the experiences of participants regarding their knowledge about the aim of orthopedic shoes, their satisfaction with communication with the pedorthist regarding wearing orthopedic shoes, their behavioral intentions, and their satisfaction with orthopedic shoes, at inclusion and 6 month after inclusion; 7) the experiences of podiatrists regarding their knowledge about motivational interviewing and their experiences and attitudes toward applying motivational interviewing in this group of patients, after all participants are included; 8) the application of motivational interviewing; and 9) foot care-related costs during 1 year follow-up. For an overview of all time points, see Table 2 (see the “Participant timeline {13}” section).

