#### Experiences of participant

A mixed methods approach will be applied to obtain the participants’ experiences and perspectives regarding their knowledge about the aim of orthopedic shoes, their satisfaction with communication with the pedorthist regarding wearing orthopedic shoes, their intentions to change wearing behavior, and their satisfaction with orthopedic shoes. A quantitative questionnaire (Monitor Orthopedic Shoes post-part (MOS) [40]) will be used to measure participant experiences on orthopedic shoes, use, and usability at 6 and 12 months after baseline. The information from the MOS will be complemented with data from in-depth interviews with 30 participants at baseline and 6 months after baseline. Participants will be selected randomly for the interviews: 15 participants of the intervention group and 15 of the control group.

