#### Time point “T0”—receiving the first pair of orthopedic shoes (baseline)

Two to 3 months after the multidisciplinary consultation, the participant will receive their first pair of orthopedic shoes during a consultation with the pedorthist. A temperature microsensor (Orthotimer®) is embedded in the insole of the orthopedic shoes for determining adherence by measuring and recording wearing time.

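### The timing of the first in-depth interview is stated inconsistently and its order relative to the first planned motivational interviewing consultation is not fixed, so in the intervention arm it may be a post-intervention measure

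*Protocol article*

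**What the plan says.** The participant-experience outcome (secondary outcome 6) covers knowledge of what the shoes are for, satisfaction with communication, intentions and satisfaction with the shoes. The protocol gives its first measurement three anchors:

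- Outcomes {12} lists "their behavioral intentions, and their satisfaction with orthopedic shoes, at inclusion and 6 month after inclusion".
- Experiences of participant describes "in-depth interviews with 30 participants at baseline and 6 months after baseline", with 15 interviewees from each arm. The timeline applies the label baseline to T0, the visit at which shoes are received: "Two to 3 months after the multidisciplinary consultation, the participant will receive their first pair of orthopedic shoes". Consent is signed at that multidisciplinary consultation.
- The section on time point −T1 says the selected participants "will be approached for an in-depth interview about their perspective on and experiences with orthopedic shoes before receiving these shoes".

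The −T1 section also schedules the intervention: "Within 1 to 6 weeks, the participant from the intervention group will have another consultation with the MI-trained podiatrist", and "The podiatrist will apply MI in this conversation". The Discussion later loosens this, allowing the MI appointment either ahead of delivery or soon afterwards.

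Under Secondary study outcome, the interview themes and how often they occur are compared between the two groups. They are then combined with the questionnaire data to help explain the adherence result.

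**The concern.** MI is meant to act on motivation and intentions, and the interview asks about these. An interview held before the first MI contact describes the participant as he or she entered the trial. One held after it describes a participant already exposed to half of the intervention. In the control arm the distinction does not arise, because control podiatrists give no MI by design. The ambiguity therefore affects one arm only.

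The interview is also the only source the text names for this outcome before shoe delivery. The companion questionnaire, the MOS, is given at 6 and 12 months in Experiences of participant, and at 6 months in the Discussion. If first-interview themes differ between arms, a reader will want to know whether the groups differed from the start or whether MI had already had an effect. The question is a real one in this trial, because allocation follows the podiatrist, is not concealed, and was not randomized for the podiatrists added later. As written, the plan does not guarantee that the interview can answer it.

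**Working it through.** The protocol gives no figure for how many interviews follow MI, so there is none to reproduce. The check compares the stated windows and then asks what each reading implies.

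**Inputs**
- Inclusion (week 0): multidisciplinary consultation with signed consent (−T1 section).
- First planned MI consultation, intervention arm: weeks 1 to 6 (−T1 section), taken here as counted from inclusion.
- Shoe receipt, T0: 2 to 3 months after the multidisciplinary consultation. With 365.25 / 12 / 7 = 4.35 weeks per month, this is 8.70 to 13.04 weeks.
- First interview: any time from week 0 to T0 (−T1 section).
- Interviewees: 15 per arm.

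**Window comparison.** The MI window (weeks 1 to 6) lies wholly inside the interview window (week 0 to week 8.70 at the earliest). The latest planned MI consultation precedes the earliest delivery by 8.70 − 6 = 2.70 weeks. No sentence orders the two events within that span.

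**Share of the 15 intervention interviews that follow MI, by reading.** MI is assumed uniform over weeks 1 to 6 (mean 3.5). For an interview uniform over weeks 0 to D, with D at least 6, the share is 1 − 3.5/D.

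| Interview timing | Share after MI | Of 15 |
|---|---|---|
| At inclusion or within week 1 | 0% | 0 |
| Uniform over weeks 0–2: (1/5) × (1/2) × (1/2) | 5% | 0.75 |
| Uniform over weeks 0–6: 1 − 3.5/6 | 42% | 6.3 |
| Uniform from inclusion to delivery at 2 months: 1 − 3.5/8.70 | 60% | 9.0 |
| Uniform from inclusion to delivery at 3 months: 1 − 3.5/13.04 | 73% | 11.0 |
| Week 6 to delivery, or at T0 | 100% | 15 |

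The first and last rows do not depend on the uniform assumption. They follow from the windows alone and correspond to wordings in the protocol: at inclusion (Outcomes {12}) and at baseline (Experiences of participant read with the T0 section). The middle rows only illustrate what lies between.

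**Effect of the Discussion.** Where the MI appointment falls after delivery, an interview held before delivery precedes it. This lowers the post-MI share for those participants and leaves the arm a mixture. The Discussion changes several visits but does not fix the date of the first interview.

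**The case against.** The strongest reply is that nothing shows the interview actually follows MI. It is described in a section about inclusion, and Outcomes {12} says at inclusion. That the −T1 text mentions MI first is only sentence order. Table 2, which carries the schedule, is not visible here and may settle the matter. This stands against any claim about frequency. A reader might infer that most intervention interviews, some 9 to 11 of 15, come after MI. That figure needs interviews to be spread evenly from inclusion to delivery, which no passage states, and the Discussion's later MI appointments would reduce it.

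Second, a reader might infer that the analysis will treat the first interview as a pre-intervention baseline and so understate the effect of MI on intentions. The documents do not support that. Secondary study outcome plans a comparison of themes between groups, with no change from baseline and no baseline adjustment. Baseline elsewhere in the protocol means shoe receipt, so the label need not mean before MI.

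Third, an interview at inclusion may not be wholly free of MI, because the MI-trained podiatrist has already seen and referred the participant. This is fair, and the remedy must allow for it.

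Fourth, exact interview scheduling is detail that a journal article may leave to the full protocol. This does not remove the point: the article states the timing, and its statements disagree on whether the measurement comes before or after the intervention.

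**Conclusion.** The point holds as an inconsistency with a specific consequence. The text followed decides whether the first interview is a pre-MI or post-MI measure in the intervention arm, and the range is 0 to 15 of 15 interviews. The lower end assumes interviews at inclusion and counts only the planned MI consultation. The upper end assumes interviews at T0 under the −T1 schedule. In controls it is MI-free by design under every reading. First-interview theme differences therefore cannot be cleanly attributed either to prior differences between arms or to MI.

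The scope is small: one qualitative secondary outcome with 15 interviewees per arm. The primary outcome, its model and the sample size are untouched. How many interviews actually follow MI cannot be determined from the document.

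**What to change.** Reconcile the timing statements in Outcomes {12}, Experiences of participant, the −T1 and T0 sections and the Discussion, so that the first interview has one anchor. Hold it at inclusion, before the planned MI consultation, with matching timing in controls.

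For interviews already held, record the interview date and the date of first MI contact, including any MI at the referral consultation. Classify each interview as pre- or post-MI, report the themes on that basis, and do not describe post-MI interviews as baseline.

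The cost is the scheduling of about 15 intervention-arm interviews, with controls timed to match, and one date variable. No extra interviews are needed.
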